### 8.6.2 Secondary Criteria

The secondary and exploratory outcome measures will not be formally analysed with hypothesis testing. The data from the secondary and exploratory outcome measures will be presented as point estimates with 95% confidence intervals. This will enable comparison of the immunogenicity of the three groups at baseline and each of the three vaccinations. As antibody titres usually display skewed distributions, geometric means (with 95% CI) will be calculated instead of arithmetic means.

[figure not shown]

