| Secondary Evaluation Criteria | 
The humoral response to the vaccine antigens will be assessed by measuring the level of
 
 
a) Total IgG and IgG isotypes on Days 0, 28, 56, 84, and 365.
 
b) Antigen specific memory B-cell by ELISPOT on Days 0, 84, and 365
 
                                                                                                                                                                                                                                                                                                                                                                                                                                                                                                                                                                                                                                                                                                                                                                  |
| Statistical Methods           | 95% confidence intervals will be calculated for incidence of adverse events and for immune responses within each group. The analysis shall be primarily descriptive.                                                                                                                                                                                                                                                                                                                                                                                                                                                                                                                                                                                                                                                                                                                                                                                                                                                                                                |

[figure not shown]

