## **1.9 Comparator Vaccine: Rabies vaccine**

### **1.9.1 Rationale for rabies vaccine**

Having a comparator vaccine is useful in Phase I trials conducted in malaria-endemic areas, since background immunity and natural exposure to malaria may make it difficult to interpret immunogenicity data. In this setting, rising titres of antibody to GMZ2 could be due to immunization or to natural exposure or both. The use of a control group will permit comparison of immune responses and will result in a clearer interpretation of serological results. While a placebo control group would accomplish this same end, using a vaccine that is beneficial to the participants further increases the benefit to risk ratio, which is always relatively low in a Phase I trial. We have chosen to use rabies vaccine as the comparator for the following reasons: i) benefit for participants who will receive rabies vaccine because they have not received this vaccine, ii) rabies vaccine is rarely used in Gabon and in Africa, iii) rabies vaccine is a protein, which is safe and well tolerated and efficacious, iv) rabies vaccine can be administered in the 0, 1 & 2 month schedule that suits the schedule of the study vaccine.

Among human infections, rabies is believed to be the tenth most common cause of death. Once clinical symptoms have occurred, the disease is almost invariably fatal. In the majority of industrialized countries, human rabies is under control, mainly due to oral vaccination of wildlife and mandatory parenteral vaccination of domestic animals. Rabies is currently an incurable disease. Antiviral agents, interferon and massive doses of rabies immune globulin have been used to treat human cases, but seem only to prolong the clinical course without affecting fatality. However, post-exposure treatment initiated at an early stage using rabies vaccine in combination with rabies immune globulin may be 100% effective in preventing death. Given pre-emptively, modern rabies vaccines produce an antibody response in over 99% of vaccinees.

[figure not shown]

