#### **Visit 1 (may take place over more than one visit)**

- Written informed consent for screening
- Medical history of participant
- Complete physical examination
- Collect 5 ml venous blood sample to measure:

[figure not shown]

- Haematology: Full Blood Count (FBC) which includes: red blood cells, platelets, white blood cell count, lymphocyte count, haemoglobin, mean corpuscular volume and mean corpuscular haemoglobin concentration, haematocrit (2.5 ml).
- Biochemistry: serum creatinine, total bilirubin, ALT, AST, alkaline phosphatase (2.5 ml).
- Blood smear for malaria parasites
- Check for inclusion and exclusion criteria
- Written informed study consent for vaccination

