### 7.2.2 Quality of the humoral Immune response:

#### Definition

The quality of the humoral immune response will be assessed by measuring, IgG1, IgG2, IgG3, IgG4 isotype responses to GMZ2 by ELISA (at Day 0 and 84).

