#### 7.2.2.2 Method and timing of measurement

The vaccine-specific IgG1, IgG2, IgG3 and IgG4 response will be assessed by ELISA for the recombinant proteins rGMZ2 expressed in *L. lactis*.

The measurements will be performed at baseline, and 4 weeks after the third vaccination (Day - 14 and 84). Experiments will be performed after Day 84.

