### 7.3.1.2 Parameters to be measured

The percentage growth inhibition will be determined as follows:

$$[(\% \text{ parasitaemia in control wells} - \% \text{ parasitaemia in test wells}) \times 100] / \% \text{ parasitaemia in control wells.}$$

The measurement will be done at baseline, after the second and the third dose of vaccination and one year after the first vaccination (at Days -14, 56, 84 and 365).

[figure not shown]

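### The immunological baseline is set at both Day -14 and Day 0, and section 8.6 rules out the between-group comparison that justifies the rabies arm

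*Protocol*

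**What the plan says.** **Baseline day.** Section 7.2.2 asks for "isotype responses to GMZ2 by ELISA (at Day 0 and 84"). Its own subsection 7.2.2.2 then says "The measurements will be performed at baseline, and 4 weeks after the third vaccination" and puts Day -14 and Day 84 in brackets. The synopsis lists "Total IgG and IgG isotypes on Days 0, 28, 56, 84, and 365". Growth inhibition is due "at Days -14, 56, 84 and 365" (7.3.1.2), and IgM and modified IgG also start at Day -14 (7.3.2). Total IgG, IFA and memory B-cell ELISPOT start at Day 0 (7.2.1.2, 7.2.3.2, 7.2.4.2).

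**Blood drawn.** The Visit 1 list in section 5.1 reads "Collect 5 ml venous blood sample to measure", followed by 2.5 ml for blood count and 2.5 ml for biochemistry. Serum for Western blot, ELISA and growth inhibition first appears at Visit 2 (Day 0), before the first dose. Section 3.1 announces five sampling points, lists six including Day -14 and Day 0, and assigns serology to all of them.

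**Analysis.** Section 1.9.1 gives the reason for the control arm: "The use of a control group will permit comparison of immune responses and will result in a clearer interpretation of serological results". Section 8.6 states that the sample size rules out comparing groups. Section 8.6.2 says "The data from the secondary and exploratory outcome measures will be presented as point estimates with 95% confidence intervals" and adds that this makes it possible to compare the three arms at baseline and after each dose. The synopsis fixes the form: "95% confidence intervals will be calculated for incidence of adverse events and for immune responses within each group".

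**The concern.** The laboratory needs one answer on which tube supplies the pre-vaccination value. A team following 7.2.2.2, 7.3.1.2 or 7.3.2 literally would look for Day -14 serum that the visit list does not provide. They would then have to substitute Day 0 ad hoc, or divert part of a biochemistry tube. Depending on which section is followed, subclasses are measured at five visits or two.

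On the analysis, section 1.9.1 argues that rising antibody may come from vaccination, natural exposure or both, and that the rabies arm is there to separate them. That separation is a between-arm quantity. Separate intervals per arm leave the reader to judge overlap by eye, and overlap is not an estimate of the vaccine effect. Section 1.8.3 also wants the two dose levels to inform dose choice, which again means setting arms against each other. Section 8.6 does not merely leave the contrast unspecified. It says that none is possible, so a later analysis plan that defined one would contradict the protocol.

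**Working it through.** **1. Baseline days set against the blood lists in section 5**

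| Assay | Baseline stated | Serum listed at that visit? |
|---|---|---|
| Total IgG (7.2.1.2) | Day 0 | yes |
| Subclasses (2.2.1, 7.2.2, synopsis) | Day 0 | yes |
| Subclasses (7.2.2.2) | Day -14 | no |
| IFA (7.2.3.2) | Day 0 | serum drawn, IFA not named |
| ELISPOT (7.2.4.2) | Day 0 | yes (PBMC tube) |
| Growth inhibition (7.3.1.2) | Day -14 | no |
| IgM, modified IgG (7.3.2) | Day -14 | no |

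Subclass schedules: Days 0, 28, 56, 84, 365 (synopsis and flow chart); Days 0, 84 (2.2.1 and 7.2.2); Days -14, 84 (7.2.2.2).

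**2. The stated blood total**

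Section 3.1 gives a maximum of about 37.5 ml. The section 5 volumes for Days -14, 0, 28, 56, 84 and 365 are 5 + 7.5 + 5 + 5 + 7.5 + 7.5 = 37.5 ml over six draws, so the plan's figure is reproduced. A further 2.5 ml immunology tube at Day -14 would make 40.0 ml. The visit-level volumes therefore use up the whole total with no such tube.

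**3. Would Day 0 serum suffice?**

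The documents give no volume per assay. The Day 0 serum tube is 2.5 ml, the same as at Day 84, where the same assays are due. Moving the Day -14 entries to Day 0 asks no more of that tube than is already asked at Day 84.

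**4. What a between-arm ratio would look like**

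Inputs: 10 per arm, three arms (section 8.2). The log10 SD of 0.4 (range 0.3-0.5) and the baseline correlation ρ of 0.5-0.8 are assumptions, because the documents give neither.

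Half-width on the log10 scale = t(0.975, df) × SD × √(1 − ρ²) × √(2/10), with df = 27 unadjusted and 26 with one covariate. The small extra term for chance baseline imbalance is ignored.

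- SD 0.4, unadjusted: 2.052 × 0.4 × 0.447 = 0.367, a factor of 2.33 either way.
- SD 0.3 and 0.5, unadjusted: factors of 1.88 and 2.88.
- SD 0.4, ρ = 0.5: 0.318, factor 2.08.
- SD 0.4, ρ = 0.8: 0.221, factor 1.66.

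The variance gain 1/(1 − ρ²) is 1.33 to 2.78, equivalent to that multiple of the sample size. If only the two arms being compared supply the variance (18 df), SD 0.3 gives 1.91 instead of 1.88, so the result hardly depends on that choice.

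**5. Why reading two intervals by eye is a poor substitute**

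Within one arm at SD 0.4, the half-width is t(0.975, 9) × 0.4/√10 = 2.262 × 0.1265 = 0.286, a factor of 1.93. Two such intervals stop overlapping only when the ratio exceeds 10^(2 × 0.286), about 3.7. The direct interval excludes 1 once the ratio exceeds 2.33.

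**The case against.** The strongest reply is that Day -14 is a stray label. Pre-dose serum is drawn at Day 0, and most sections, the synopsis and the flow-chart row for IgG and isotypes all start there. Two of the three affected assay groups are exploratory, and 7.3.1.1 defers growth inhibition until the assay is validated. This is right about the size of the problem, and a reader who infers that the trial has no usable baseline, or no pre-vaccination sample for some endpoints, goes too far. The contradiction still needs removing.

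Nor is it settled that no serum is available at Day -14. Section 3.1 places serology there. The 37.5 ml total also equals five draws at the 7.5 ml maximum, and the flow chart numbers five samples beginning at Day -14, with none numbered at Day 0. The total alone therefore does not decide the matter. The itemised visit lists are the more specific text, and they leave Day -14 without an immunology tube.

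On analysis, a reader might infer that the plan ignores baseline and the control arm. It does not. Section 8.6.2 presents all three arms at baseline and after each dose, and 7.2.1.1 promises mean ratios with intervals, though without saying of what to what.

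It can also be said that the choice of model belongs in the statistical analysis plan. For the model's details that is fair. It does not rescue the 8.6 sentence, which conflicts with 1.9.1 and 8.6.2. Section 8.7.1 ties the analysis plan to the database lock for the final analysis, whereas section 3.1 schedules the primary analysis of all primary and secondary endpoints at Day 84, so the protocol does not guarantee a plan before that readout.

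**Conclusion.** The point holds on two counts. The baseline day contradicts itself between sections, and for subclasses within one section. The statement that groups cannot be compared contradicts both the rationale for the rabies arm and the immunogenicity section, and the stated output is within-group intervals with no baseline-adjusted or versus-control contrast.

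The schedule finding rests on the text and on the 37.5 ml sum. The precision figures rest on the assumed SD and correlation. Under them a Day-84 ratio is known to within a factor of about 2.3 (1.9-2.9) unadjusted, and about 2.1-1.7 at SD 0.4 after adjustment. A sample of 10 per arm makes a ratio imprecise but does not prevent its estimation.

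The adult medians in section 1.7.4.1 should not be used to size the role of natural exposure here. They set semi-immune Gabonese adults against vaccinated malaria-naive German adults, and do not measure what children aged 1-5 acquire in 84 days.

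This should be corrected, but it does not touch the primary safety objective.

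**What to change.** - Name Day 0 (pre-dose) as the single immunological baseline in 7.2.2.2, 7.3.1.2 and 7.3.2.
- Correct section 3.1 so that the number of sampling points matches the list and serology is not assigned to Day -14. Align the numbered samples in the flow chart with it.
- State one subclass schedule and use it in the synopsis, flow chart, 2.2.1, 7.2.2 and 7.2.2.2.
- Replace the 8.6 sentence that rules out comparison with a statement that no formal hypothesis tests between groups will be done for immunogenicity.
- In 8.6.2 add, as estimation only, the Day-84 geometric mean ratio of each GMZ2 dose to rabies, and of 100 to 30 µg, with 95% intervals. Take these from a linear model of log antibody level on arm and log Day-0 level. Keep the within-group geometric means, and define or delete the mean ratios in 7.2.1.1. Further model detail can go in the statistical analysis plan.

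The cost is wording plus one model on data already collected, with no change to planned blood volumes. The drawback is wide intervals, which should be labelled descriptive so that an interval containing 1 is not read as absence of a response.

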## 8.7 Data Management

Throughout regular data collection and monitoring, clinical data reported on CRFs and/or relevant serological/biological sample analysis results scheduled in the protocol will be integrated into the internal clinical data management system.

For each batch of data, double entry, quality control and triggers to computerised logic and/or consistency checks will be systematically applied in order to detect errors or omissions. Moreover, the clinical trial monitor will check through and verify 100% data on CRF with source documents, and all identified errors will be corrected. After integration of all corrections in the complete set of data, the database will be locked and saved before being released for statistical analysis. Each step of this process will be monitored through the implementation of individual passwords and/or regular backups in order to maintain appropriate database access and to guarantee database integrity.

### 8.7.1 Plans for analysis

A final statistical analysis plan will be agreed upon by the investigators, AMANET and EMVI prior to locking of the database for the final analysis. However, an interim analysis is planned at 28 days post dose 3 (after day 84). This analysis will allow AMANET and EMVI make decisions for the next trial based on the immediate safety profile. This analysis will include information on adverse events by dose and number of vaccinations. Thereafter, the study will continue in a single blind manner for additional safety surveillance and immunogenicity assessment. This additional information will be appended to the study report.

It is anticipated that the results of this study will be presented to the scientific community via oral presentations at meetings and written publications in scientific journals. The data to be presented and the authorship will be discussed between investigators and the sponsor. It is AMANET policy to have the Principal Investigator lead the authorship for work arising from clinical trials, however, the draft manuscript has to be, approved by the sponsor and EMVI prior to any official communication.

The official report of the primary analysis will be submitted through appropriate channels and upon approval by AMANET. This report will contain detailed information about the participants, their tolerance of the vaccines, their side effects and laboratory abnormalities, as well as their overall immune responses to vaccination based on the ICH E-3 and E-9 format.

### 8.7.2 Source documents and access

Information that cannot be collected initially onto CRFs, namely, clinical laboratory test results and adverse event medical records; screening sheets will first be collected onto separate source documents prior to transcription into CRFs. Only authorized study personnel and study the monitors will have access to CRFs and other source documents, and access to these documents will be controlled by the Clinical Coordinator. The official AMANET source document agreement form which lists the classes of documents will be signed and maintained on the investigator file, including the home visit follow-up diary cards.

### 8.7.3 Data ownership

The results emanating from this study primarily belongs to the AMANET/EMVI. However, a consortium comprising the investigators, AMANET (study sponsor), and EMVI (product owner) shall corporately work towards development and licensure of GMZ2.

[figure not shown]

## 9 SITE MONITORING PLAN

Site monitoring will be conducted by a qualified and experienced clinical monitor appointed by AMANET to ensure that ICH-GCP standards and regulatory guidelines are being followed. Pre-trial monitoring visits will be made to the site, including the clinical laboratory. All records will be made available to monitors, including regulatory files, CRFs and other source documents, QA/QC documentation, SOPs, etc. An agreed site monitoring schedule will be reached before study start, but at the discretion of the monitor, additional site visits may be made during the course of the trial and at the end of the surveillance period.

The monitoring plan will include the number of participant charts to be reviewed, which/what proportion of data fields and what will be monitored, and who will be responsible for conducting the monitoring visits, and who will be responsible for ensuring that monitoring findings are addressed.

Before each monitoring visit, the monitor will contact the principal investigator and send a proposed visit agenda for discussion. During the visit, the monitor will undertake 100% source document verification, check all informed consent documents, and inspect site facilities, state of equipment maintenance, vaccine accountability and specimen storage documents, and general compliance of investigators to ICH-GCP.

For each visit, a detailed monitoring report on the standard forms shall be provided within two weeks, together with a specific action items summary. This report will be reviewed by two representatives from GMZ2 Clinical Development Team and any issues arising will accordingly be followed up.

[figure not shown]

## **10 QUALITY CONTROL AND QUALITY ASSURANCE**

### **10.1 QA/QC Policy**

SOPs for quality management which have been in existence and use will be reviewed and updated and used to train appropriate personnel, and kept on file with documentation of the training. Data will be evaluated for compliance with protocol and accuracy in relation to source documents. The study will be conducted in accordance with procedures identified in the protocol. The types of materials to be reviewed, who are responsible, and the schedule for reviews will be referenced in the SOPs. Study-specific training will be provided for all staff prior to the commencement of the trial.

Regular monitoring will be performed according to ICH-GCP. Following written SOPs, the monitors will verify that the clinical trial is conducted and data are generated, documented (recorded), and reported in compliance with the protocol, ICH-GCP, and the applicable regulatory requirements. Reports will be submitted to AMANET on monitoring activities and specific recommendations will be implemented to improve the quality of the study. The MRU at Lambaréné will implement quality control procedures beginning with form design, training, tracking system, data entry system and generate data quality control checks that will be run on the database. Any missing data or data anomalies will be communicated to the field site for clarification/resolution.

The investigational site will provide direct access to all trial related source data/documents, and reports for the purpose of monitoring and auditing by the sponsor, and inspection by local and regulatory authorities as the case may be.

### **10.2 Modification/Amendment of the Protocol**

No amendments to this protocol will be made without consultation with, and agreement of, the sponsor. Any changes that appear necessary during the course of the trial must be discussed by the investigator and sponsor concurrently. If agreement is reached concerning the need for an amendment, it will be produced in writing by the sponsor and/or the investigator and will be made a formal part of the protocol. An amendment may require IEC/IRB approval. All amendments must also be transmitted to Regulatory Authorities, if applicable.

An administrative change to the protocol is one that modifies administrative and logistical aspects of a protocol but does not affect the subjects' safety, the objectives of the trial and its progress. An administrative change does not require IEC/IRB approval. However, the IEC/IRB must be notified whenever an administrative change is made. All amendments involving a change in the study procedure must seek for approval. All amendments involving a change in the study procedure must seek for approval.

The investigator is responsible for ensuring that changes to an approved trial, during the period for which IEC/IRB approval has already been given, is not initiated without IEC/IRBs review and written approval except to eliminate apparent immediate hazards to the subject

